### [Information to be collected at the time of termination or cancellation]

| Item | Detail |
| --- | --- |
| Treatment-related factors | Chemotherapy start ~ end date, whether or not chemotherapy has been completed, use of analgesics, use of local anesthetics (sputum, jelly, etc.), use of opioids, neutrophil count (lowest during treatment), lymphocyte count (lowest during treatment), albumin (lowest value during treatment), creatinine (highest value during treatment), presence and timing of use of GCF-S preparations, PNI |
| Oral mucositis | Presence and grade of oral mucositis (CTCAE v3.0 and v5.0), and date of onset in cases |
| Candida onset | Presence and date of onset |
| Drugs for Research Use | Usage  Presence or absence of adverse events related to the study drug (inflammatory changes such as redness and swelling of the oral mucosa) |
| Adverse events | Presence or absence of the development of taste disorders, oral infections and other adverse events |

- 1. Treatment after the end of the study

The betamethasone gargle used in this study is not covered by insurance for the treatment of oral mucositis. Therefore, it will not be possible to continue the same treatment after the study concludes. After the study, the best alternative treatment will be selected from those available under insurance coverage, with the aim of minimizing any potential disadvantages.

- 1. Provision of test results, etc. to research subjects

As the study results do not directly impact the participants' subsequent treatment, the results will not be provided to the participants unless they request them.

- 1. Discontinuation criteria in individual study subjects [Discontinuation criteria]
- If the participant requests to discontinue their participation.
- If the occurrence of an adverse event (e.g., exacerbation of the primary disease, emergence of complications, development of a new disease) leads the investigator to determine that continuing the study is no longer appropriate for the participant.
- If, for any other reason, the investigator determines that continuing the study is not appropriate for the participant.

[Post-Discontinuation Procedures]

If discontinuation occurs, the use of the betamethasone gargle will be immediately stopped. The participant will then transition to a post-study observation period, with follow-up until the final visit whenever possible. Appropriate alternative treatments will be considered for each participant after discontinuation, and treatment will be adjusted accordingly.

# Predicted benefits and disadvantages for the study subject

- 1. Projected Profits

Participation in this study may reduce the incidence of oral mucositis caused by betamethasone. Additionally, the findings from this study could potentially contribute to the advancement of medical care in the future.

- 1. Foreseeable disadvantages

There are no direct risks associated with participation in this study; however, allergic reactions such as rashes or hypersensitivity to betamethasone may occur. Additionally, side effects such as the development of oral candidiasis or exacerbation of oral infections may occur. In case these side effects arise, gargling with betamethasone will be immediately discontinued, the participant will gargle with water, and antifungal or antibacterial treatments will be considered if necessary.

- 1. Expected side effects Hypersensitivity reactions to betamethasone Development of oral candidiasis Exacerbation of oral infections
  2. Expected side effects Not applicable

# Treatment if not participating in the present study

The investigational drug used in this study is not covered by insurance for the condition being treated. Therefore, if a participant does not join the study, treatment will be selected from available therapies covered by insurance and provided to the patient.

Potential treatments include azulene gargle or dexamethasone ointment.

When determining the treatment, the benefits and risks of the medical options will be explained to the patient before proceeding with the treatment.

| Treatment methods | Features and Efficacy | Typical side effects |
| --- | --- | --- |
| Aznol mouthwash | Anti-inflammatory effect | Hypersensitivity |
| Dexamethasone ointment | Symptomatic relief of stomatitis | Allergies, oral infections |

# Target number of cases

296 participants (148 participants in the betamethasone gargle group, 148 participants in the azulene gargle group)

[Rationale for setting]

Assuming an incidence rate of 40% for oral mucositis during chemotherapy for malignant tumors, a previous study by Kuba et al. showed that the risk of developing oral mucositis with steroid gargles is reduced to 0.68 times, i.e., 27%. Using two tailed alpha of 0.2, a power of 0.8, and accounting for a 10% dropout rate, the target sample size was set to 296 participants (148 in the intervention group and 148 in the control group).

# Duration of the study

Study Duration: From the JRCT publication date to December 31, 2026

Case Registration Period: From the JRCT publication date to March 31, 2026 Case Report Form Submission Deadline: June 30, 2026

# How to Register a Case

The principal investigator or co-investigator of the research site shall fill in the necessary items on the "Study Subject Screening List (Correspondence Table)" after obtaining written consent from the research subject.

The responsible investigator or co-investigator at the participating medical institution will obtain written informed consent from the participant and fill in the required information on the "Participant Screening List (Correspondence Table)."

The responsible investigator or co-investigator will confirm that the participant meets all inclusion criteria and none of the exclusion criteria, then complete the case registration form. The completed form will be emailed to the data management representative, , Kyushu Dental University.

・Patient registration address

・Name of institution: Kyushu Dental University, Department of Oral Health,

at Kyushu Dental University will review the case registration form. If the participant is deemed eligible, a registration confirmation letter with the registration number and allocation result will be issued. The confirmation letter will be emailed to the responsible investigator or co-investigator at the participating medical institution.

If the participant is deemed ineligible, will notify the responsible investigator or co- investigator with the reason for ineligibility.

The responsible investigator or co-investigator will verify the case registration confirmation letter received and initiate the betamethasone gargle or azulene gargle as indicated in the confirmation letter.

# Randomization Method and Allocation Adjustment Factors

Randomization Method: Participants will be randomly allocated in a 1:1 ratio to the betamethasone gargle group or azulene gargle group using computer software (stratified block randomization).

Allocation Factors: Presence of oral mucositis risk drugs (High risk: Drugs with an oral mucositis incidence rate of 30% or more as stated in the drug package insert).

Registration and Allocation Institution: Kyushu Dental University

# Managing Blinding

- 1. Methods of blinding Not applicable
  2. Determination and procedure for the need for key opening (key opening) Not applicable

## Evaluation items

- 1. Primary endpoint

## The presence of Grade 1 oral mucositis and the date of onset.

- 1. Secondary endpoints

Grade 2 and 3 oral mucositis onset and date of onset Oral candidiasis onset and date of onset

Completion of drug therapy

- 1. Safety endpoints

The presence of Grade 2 or 3 oral mucositis and the date of onset. The onset of oral candidiasis and the date of onset.

Whether the participant completed the pharmacotherapy.

# Statistical analysis

The analysis population and its definition are outlined below. The analysis population will be presented in a flowchart in accordance with the CONSORT statement.

| Population to be analyzed | Definition |
| --- | --- |
| Enrollment example  Intention To Treat (ITT) | All study subjects randomly assigned to the study |
| Population to be analyzed for safety analysis  Safety Analysis Set (SAS) | All study subjects for whom study medications were used |
| Largest Population Analyzed  Full Analysis Set (FAS) | Study subjects with ITT for whom a study drug was used and the primary endpoint was obtained |
| Target population that conforms to the research protocol  Per Protocol Set (PPS) | Study subjects with FAS who do not deviate from the research protocol. |

- 1. Identify the target population

【**Analysis Populations**】ITT,FAS,PPS

Summarize patient background using summary statistics.

| Population to be analyzed | Definition |
| --- | --- |
| Enrollment example  Intention To Treat (ITT) | All study subjects randomly assigned to the study |
| Largest Population Analyzed  Full Analysis Set (FAS) | Study subjects with ITT for whom a study drug was used and the primary endpoint was obtained |
| Target population that conforms to the research protocol  Per Protocol Set (PPS) | Study subjects with FAS who do not deviate from the research protocol. |

- 1. Primary endpoint analysis

【**Analysis Population**】FAS,PPS

Estimate the risk difference and risk ratio, along with their 95% confidence intervals, for the incidence of grade 1 oral mucositis between the betamethasone gargle group and the azulene gargle group. Based on the settings from the prior sample size calculation, a p-value < 0.2 derived from Fisher’s exact test will be considered statistically significant. The cumulative incidence at each time point will be estimated using the Kaplan–Meier method, and for reference, a log-rank test will be performed.

- 1. Analysis of secondary endpoints

【**Analysis Population**】FAS,PPS

1. Descriptive statistics will be used to summarize each evaluation criterion.
2. Estimate the risk difference and risk ratio, along with their 95% confidence intervals, for the incidence of grade 2 oral mucositis between the betamethasone gargle group and the azulene gargle group. Based on the settings from the prior sample size calculation, a p-value < 0.2 derived from Fisher’s exact test will be considered statistically significant. The cumulative incidence at each time point will be estimated using the Kaplan–Meier method, and for reference, a log-rank test will be performed. The incidence rate of oral candidiasis in the betamethasone gargle group and the azulene gargle group will be calculated using the Kaplan-Meier method, and the difference between the two groups will be analyzed using the log-rank test.
3. Factors associated with the incidence of oral mucositis for each grade will be analyzed using Cox regression analysis.
   1. Analysis of Safety Assessment

The adverse events in the betamethasone gargle group and the azulene gargle group will be described.

- 1. Subpopulation analysis Not applicable
  2. Interim Analysis Plan Not implemented
  3. Handling of missing data, etc.

In cases where some data points for investigation items are missing, those cases will not be discarded, and the data will still be included in the statistical analysis.

- 1. Changing the Statistical Analysis Plan

If any changes to the original statistical analysis plan are made during the study, the research protocol or statistical analysis plan will be revised, and the changes will be explained in the final study report.

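### The primary test, a pooled Fisher's exact test at p < 0.2, cannot use the stratification factor and is conservative; the planned 80% power is met, but a stratified test would do better at the same N

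*Protocol*

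**What the plan says.** Protocol, Randomization Method and Allocation Adjustment Factors: participants are allocated 1:1 "using computer software (stratified block randomization"). There is one allocation factor with two levels, defined as "High risk: Drugs with an oral mucositis incidence rate of 30% or more" according to the package insert, against all other drugs.

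Protocol, Statistical analysis, Primary endpoint analysis: the arms are compared by risk difference and risk ratio with 95% confidence intervals, and the decision rule is that "a p-value < 0.2 derived from Fisher’s exact test will be considered statistically significant". That threshold is tied to the sample size settings. A Kaplan-Meier estimate and a log-rank test are added, the latter for reference only. The same Fisher rule is repeated for grade 2 mucositis under the secondary endpoints. No stratum is mentioned in either place.

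Protocol, Target number of cases: "Assuming an incidence rate of 40% for oral mucositis during chemotherapy for malignant tumors", which on steroid gargle "is reduced to 0.68 times, i.e., 27" per cent. The calculation is made "Using two tailed alpha of 0.2, a power of 0.8, and accounting for a 10% dropout rate" and gives 296 participants, 148 per arm.

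**The concern.** The allocation factor is defined by the drug's known rate of the outcome being studied, so it can be expected to be prognostic. When arms are balanced on a prognostic factor and the factor is then left out of the test, the between-stratum variation stays in the variance although the design has removed it from the treatment comparison. The test then rejects less often under the null than its nominal level.

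Fisher's exact test adds a separate source of conservatism, because its p-values are discrete and it guarantees a size no greater than nominal.

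Both effects push the true false-positive rate below 0.2. This exploratory phase II trial chose an alpha of 0.2 deliberately, to gain sensitivity. A decision test that runs at 0.12 to 0.16 gives part of that back. At stake are efficiency and precision, not validity: the error is on the safe side.

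**Working it through.** **1. The plan's sample size.** Inputs, all from Target number of cases: p1 = 0.40, p2 = 0.27, two-sided alpha 0.2 (z = 1.2816), power 0.8 (z = 0.8416), dropout 10%. The mean risk is 0.335 and the difference d = 0.13.

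n = [1.2816 × √(2 × 0.335 × 0.665) + 0.8416 × √(0.40 × 0.60 + 0.27 × 0.73)]² / 0.13² = (0.8554 + 0.5564)² / 0.0169 ≈ 117.9, so 118 per arm.

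With the continuity correction: n' = (n/4) × [1 + √(1 + 4/(n × d))]² = (117.9/4) × (1 + 1.1229)² ≈ 132.9, so 133 per arm. Then 133/0.9 = 147.8, so 148 per arm and 296 in total.

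The stated figure reproduces exactly, but only with the continuity correction (without it: 132 per arm after dropout). The corrected formula approximates Fisher's test, so the sample size already pays for that test's conservatism.

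**2. Fisher's test with no stratum effect.** Full enumeration of two binomials with 133 per arm, rejecting when p < 0.2:

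- Size: 0.152 at a common risk of 40%, 0.162 at 33.5%, 0.154 at 27%. The maximum over risks from 5% to 95% is 0.163.
- Power: 0.805 for 40% against 27%. With the unrounded 0.68 × 40% = 27.2% it is 0.795.
- At 148 per arm (no dropout) the power for 40% against 27% is 0.834.

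**3. Effect of the stratum.** The protocol gives no stratum risks or shares. Assumed here: two equal strata, arms balanced within each, control risks averaging 40%, and a common risk ratio of 0.27/0.40 = 0.675. For size, both arms carry the control risks.

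The CMH statistic is [Σ(a − E)]² / ΣV over strata. Here a is the number of events in one arm of a stratum, E = m × n₁/N and V = n₁ × n₀ × m × (N − m) / [N² × (N − 1)], with m events among N participants, n₁ and n₀ of them in the two arms. It rejects above 1.2816² = 1.642. The unstratified chi-square test is shown to separate the two sources of loss.

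| Control risks in strata | Size: Fisher | Size: chi-square | Size: CMH | Power: Fisher | Power: chi-square | Power: CMH |
|---|---|---|---|---|---|---|
| 40% / 40% | 0.152 | 0.192 | 0.192 | 0.805 | 0.840 | 0.839 |
| 50% / 30% | 0.142 | 0.182 | 0.197 | 0.809 | 0.844 | 0.848 |
| 60% / 20% | 0.116 | 0.153 | 0.198 | 0.821 | 0.857 | 0.869 |

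The first row is exact apart from CMH; the rest is simulation with 400,000 runs per scenario. An extreme split of 70%/10% gives Fisher size 0.068 and power 0.845, against 0.199 and 0.916 for CMH.

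**4. Which source matters.**

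- Power, Fisher to chi-square: 0.844 − 0.809 = 3.5 points at 50/30 and 0.857 − 0.821 = 3.6 at 60/20.
- Power, chi-square to CMH: 0.4 and 1.2 points.
- Size, Fisher to chi-square: 4.0 points at 50/30 and 3.7 at 60/20.
- Size, chi-square to CMH: 1.5 and 4.5 points.

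So Fisher's conservatism dominates the power gap in both scenarios. It also dominates the size gap at 50/30, while at 60/20 ignoring the stratum contributes slightly more.

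**5. Precision of the risk difference.** The pooled variance term is 0.24 + 0.1971 = 0.4371. The within-stratum terms are as follows.

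- 50/30: (0.25 + 0.21)/2 + (0.3375 × 0.6625 + 0.2025 × 0.7975)/2 = 0.4225. The standard error ratio is √(0.4371/0.4225) = 1.017.
- 60/20: (0.24 + 0.16)/2 + (0.405 × 0.595 + 0.135 × 0.865)/2 = 0.3789. The ratio is 1.074.

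A risk difference that ignores the stratum therefore has a standard error about 2% to 7% too large.

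**The case against.** The strongest reply is that the plan delivers what it promises. The sample size carries the continuity correction, the test is the one that correction approximates, and the power is 0.805. A reader might infer that the trial is underpowered because the test ignores the strata. The documents do not support that: on the plan's inputs Fisher's power is at or above 80% in every scenario above, and it rises as the strata diverge. Only the unrounded 27.2% brings it to 0.795 with no stratum effect, and that comes from rounding in the assumption, not from the strata.

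A reader might also blame the whole shortfall in size on the missing stratification. That is not right either. With no stratum effect the size is already 0.15 to 0.16, and the further drop depends on stratum risks that the protocol does not give. A 30% cutoff says on which side a drug falls, not how far apart the two groups are.

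Nor can it be said that the log-rank test or the Cox analysis is unstratified. The protocol is silent, the log-rank test is for reference, and such detail is commonly left to the statistical analysis plan, which is not at hand.

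Finally, an exact test is defensible in an exploratory trial, and its error is conservative. Fisher's test guarantees its level, whereas CMH holds it only approximately: a 55%/25% split gave a simulated size of 0.206.

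All of this stands, and it limits the point to efficiency. It does not remove the point. The protocol itself names the decisive test and its threshold, and that test cannot use the factor on which allocation was balanced.

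**Conclusion.** The point holds as a matter of efficiency. The primary test ignores the allocation factor and is conservative: true size is about 0.15 to 0.16 against a stated 0.2 with no stratum effect, and about 0.14 to 0.12 with control risks of 50/30 to 60/20. Type I error is not inflated and the planned 80% power is met, so no stated figure is missed.

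At the same N, a stratified CMH test without continuity correction brings the size to about 0.19 to 0.20 and gives power of about 0.84 to 0.87. That is a gain of 3.4 to 4.8 points in the tabulated scenarios, most of it from no longer using Fisher's test as the decisive one. The rest grows with how prognostic the stratum proves to be.

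The figures without a stratum effect rest on the protocol's own inputs. Those with one rest on assumed stratum risks, equal strata and a common risk ratio. The change is worth making before results are known, but nothing in the trial fails without it.

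**What to change.** In Primary endpoint analysis, name the CMH test stratified by the allocation factor, two-sided at 0.2 and without continuity correction, as the primary test. Report the Mantel-Haenszel risk difference and risk ratio with 95% confidence intervals, and keep the pooled Fisher test as a sensitivity analysis. Make the same change for grade 2 mucositis under the secondary endpoints. Where the log-rank test and Cox model are specified in detail, use the same stratum.

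The cost is wording only. The stratum is needed for allocation, so it is already recorded, and the target stays at 296. The protocol already provides for revising the analysis plan. Because the trial is open-label, the revision should be dated before any comparison of outcomes by arm.

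### Oral candidiasis is a declared safety endpoint, but its only between-arm comparison is assigned to the FAS and PPS, which may omit treated cases

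*Protocol*

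**What the plan says.** Four parts of the protocol bear on this point.

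- **Endpoint.** Evaluation items lists candidiasis under the secondary endpoints and again under the safety endpoints: "The onset of oral candidiasis and the date of onset".
- **Expected harm.** Predicted benefits and disadvantages warns that "side effects such as the development of oral candidiasis or exacerbation of oral infections may occur". Research Background gives fear of candidiasis as one reason why topical steroids were not widely adopted.
- **Populations.** Statistical analysis defines a Safety Analysis Set, labelled as the population for safety analysis: "All study subjects for whom study medications were used". The FAS is narrower: "Study subjects with ITT for whom a study drug was used and the primary endpoint was obtained". The PPS is narrower again: "Study subjects with FAS who do not deviate from the research protocol".
- **Analyses.** The secondary-endpoint analysis is headed "Analysis Population】FAS,PPS". Its second item states: "The incidence rate of oral candidiasis in the betamethasone gargle group and the azulene gargle group will be calculated using the Kaplan-Meier method". It adds that "the difference between the two groups will be analyzed using the log-rank test". The safety section says only that adverse events in the two groups will be described. It names no population, does not mention candidiasis and sets no comparison.

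**The concern.** Harm is normally compared in everyone exposed. This protocol defines that population and then assigns the comparison of a declared safety endpoint to two efficacy populations. Whether a participant enters the FAS depends on having a mucositis result, which has no bearing on whether candidiasis occurred. Whether a participant enters the PPS depends on adherence, which candidiasis or its treatment could affect. No analysis section names the Safety Analysis Set, and the table repeated under identification of the target population leaves it out.

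At stake is the one harm that the background singles out. There is no safety evaluation committee and no interim analysis, so the final analysis is the only planned between-arm look at it. For mucositis the protocol asks for a risk difference and a risk ratio with 95% intervals. For candidiasis it asks for a Kaplan-Meier rate in each arm and a log-rank test, with no between-arm estimate. This is a stated population rule, so it is not a detail left to the statistical analysis plan.

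**Working it through.** **Step 1: who is in each set**

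| Treated participant | Safety Analysis Set | FAS | PPS |
|---|---|---|---|
| Mucositis endpoint obtained, no deviation | in | in | in |
| Mucositis endpoint obtained, deviation | in | in | out |
| Mucositis endpoint not obtained | in | out | out |

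The candidiasis comparison uses the last two columns only. The missing-data rule keeps cases with some missing items, but it does not restore people whom the FAS definition excludes.

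**Step 2: inputs from the protocol**

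Target number of cases gives 148 per arm, incidences of 40% and 27%, two-sided alpha 0.2, power 0.8 and 10% dropout. The figure reproduces: 118 per arm without continuity correction, 133 with it, and 133 / 0.90 = 147.8, rounded up to 148. It is used here only to fix the scale. Planned loss is 0.10 × 148 = 14.8, about 15 per arm, which leaves 133.

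**Step 3: assumptions**

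The documents give no candidiasis rate and no expected number of treated participants outside the FAS. I assume that all 148 in an arm are treated, that 15 lack the mucositis endpoint, and that the candidiasis rate inside the FAS is f = 10% or 5%. The rate q among the 15 excluded is varied. These are crude proportions, not Kaplan-Meier estimates.

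**Step 4: formula and results for one arm**

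Rate in all treated = (133 × f + 15 × q) / 148. The shift from the FAS rate is (15/148) × (q − f).

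| q among the 15 excluded | All treated, f = 10% | All treated, f = 5% |
|---|---|---|
| 0% | 13.3/148 = 9.0% | 6.65/148 = 4.5% |
| equal to f | 14.8/148 = 10.0% | 7.4/148 = 5.0% |
| 20% | 16.3/148 = 11.0% | 9.65/148 = 6.5% |
| 40% | 19.3/148 = 13.0% | 12.65/148 = 8.5% |
| 60% | 22.3/148 = 15.1% | 15.65/148 = 10.6% |

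The shift runs from about −1.0 to +5.1 percentage points at f = 10%, and from −0.5 to +5.6 at f = 5%. It is zero when q = f.

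**Step 5: the between-arm difference**

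The error in the difference is the betamethasone shift minus the azulene shift. Suppose f = 10% in both arms, with q = 40% under betamethasone and 10% under azulene. The FAS then shows no difference, while all treated participants show 13.0% − 10.0% = 3.0 points. If the two values of q are swapped, the sign reverses.

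**The case against.** The strongest reply is that little would be lost in practice.

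- Mucositis and candidiasis are recorded together, at each visit after allocation and at termination or cancellation. A visit that records candidiasis should also record mucositis. After discontinuation, follow-up continues to the final visit where possible.
- The protocol does not say that an obtained endpoint means complete eight-week status. If any post-allocation assessment counts, few treated participants would leave the FAS.
- Candidiasis is not itself a discontinuation criterion. Suspending the betamethasone gargle for it, as the treatment criteria direct, is not a deviation and removes nobody from the PPS. The FAS keeps deviators in any case. (The section on foreseeable disadvantages describes immediate discontinuation instead. The two passages should be reconciled, not least because the PPS depends on what counts as a deviation.)
- The adverse-event definition is broad enough to cover candidiasis, and the Safety Analysis Set is labelled for safety analysis. A descriptive summary may therefore still show every treated case.

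All of this stands, and it limits the likely size of the problem. None of it changes the population rule: the comparison is tied to the FAS and PPS, and the descriptive summary has no stated population and compares nothing.

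A reader might go further and infer that participants with candidiasis are more likely to be excluded, so that a large part of the rate would vanish. The documents do not support this. It would require many cases but few non-cases to lose the mucositis endpoint, and nothing in the protocol says so. If loss is unrelated to candidiasis, there is no expected shift.

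**Conclusion.** The point holds as an error of assignment. A declared safety endpoint is compared only in populations that can omit treated participants, although a suitable population is defined and left unused. Whether this understates harm is unknown. It does so within an arm only if candidiasis is more frequent among those excluded, and the between-arm difference depends on how exclusions fall in both arms. Under the assumed 15 of 148 outside the FAS and a 10% rate inside it, the rate in all treated participants is 9.0% to 15.1%. That range shows how sensitive the result could be and is not a forecast.

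Two further readings should not be drawn. The protocol nowhere says that a non-significant log-rank test will be taken as absence of risk. Nor do the documents give a margin against which an upper confidence limit could be judged, so no decision criterion of that kind follows from them. The change is worth making before the data are analysed, because it is cheap and concerns the harm that the background itself raises. It does not threaten the primary analysis.

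**What to change.** In the analysis sections, name the Safety Analysis Set, grouped by gargle received, as the main population for the candidiasis Kaplan-Meier and log-rank analysis. Add the between-arm difference in cumulative incidence with a 95% interval, in line with the risk difference and interval already planned for mucositis. Keep the FAS, and the PPS if wanted, as supportive. State in the safety section that adverse events are described in the Safety Analysis Set, and add that set to the repeated population table.

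The cost is a few lines of wording and one extra table. Candidiasis onset and its timing are already collected at visits and at termination or cancellation, so no new data are needed and the sample size does not change.

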If oral candidiasis occurs during the treatment, gargling will be suspended in the betamethasone group and resumed once the candidiasis resolves. In the azulene group, gargling will continue even if oral candidiasis is detected.

- 1. Concomitant treatment

No specific concurrent drugs or therapies are mandatory for this study.

- 1. Prohibited Drugs / Devices / Therapies

The use of steroid ointments on the oral mucosa is prohibited during the study period.

- 1. Combined use of limiting shalf/combined use of limiting machine/combined use of limiting therapy

There are no restricted drugs or therapies defined for this study.

- 1. Assessments, collection items and schedules
- Schedule (Table)

|  | Regustration/assignment | Medical examination | | | | At exit | At the time of cancellation |
| --- | --- | --- | --- | --- | --- | --- | --- |
|  |  | 1~2 weeks | | | | Week 8 ends |  |
| Obtaining  consent | ● | － | － | － | － | － | － |
| Allocation | ● | － | － | － | － | － | － |
| Information gathering 1 | ● | － | － | － | － | － | － |
| Information gathering 2 | － | ● | ● | ● | ● | － | － |
| Information gathering 3 | － | － | － | － | － | ● | ● |

*1 The date of registration can be before or after the start of chemotherapy. The date of registration and the date of allocation can be different days.

*2 Once a week for inpatient treatment or at the time of hospitalization, and on the day of treatment for outpatient treatment

In the case of postponement of cool, inclusion and information gathering will be carried out according to the postponement

Dental examinations are not mandatory, and dentists are allowed to visit outpatient chemotherapy rooms for examinations

- Observation and Inspection Items

[Items to be collected at the time of registration]

| Item | Detail |
| --- | --- |
| Patient  Background | Age, sex, anamnesis and medication administered, primary site, smoking  history, alcohol consumption history, weight |
| Treatment-  related factors | The day of the start of treatment, the name of the anti-cancer drug, and the  use of drug/ combined therapy |
| Clinical laboratory findings (In-hospital  examination) | Neutrophil count, lymphocyte count, albumin, creatinine |

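### The only between-arm comparison of oral candidiasis, a listed safety endpoint, is set in the FAS and PPS rather than in all treated participants, and could be biased in either direction

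*Protocol*

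**What the plan says.** The protocol's Evaluation items list candidiasis twice, as a secondary endpoint and as a safety endpoint ("The onset of oral candidiasis and the date of onset"). The sections on foreseeable disadvantages and on predictable diseases both name it as an expected harm.

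The Statistical analysis section defines three sets that matter here:

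- **Safety Analysis Set:** "All study subjects for whom study medications were used". Its label says that it is for safety analysis.
- **FAS:** "Study subjects with ITT for whom a study drug was used and the primary endpoint was obtained".
- **PPS:** FAS members without a protocol deviation.

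The candidiasis comparison is in item 2 of the analysis of secondary endpoints: "The incidence rate of oral candidiasis in the betamethasone gargle group and the azulene gargle group will be calculated using the Kaplan-Meier method", with a log-rank test between groups. The population line of that section names the FAS and PPS. The section on analysis of safety assessment says only that adverse events will be described by group, and has no population line.

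Under the criteria for protocol treatment, candidiasis leads to suspension and later resumption of gargling in the betamethasone group. For the control group the rule differs: "In the azulene group, gargling will continue even if oral candidiasis is detected".

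**The concern.** A harm is normally compared in everyone exposed, so that no treated case is lost for a reason unrelated to whether the harm occurred. Here the protocol fixes two narrower sets for the comparison. One depends on a different outcome having been obtained. The other depends on adherence to instructions that take effect only once the harm has occurred and that differ between arms.

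The background section gives concern about candidiasis as one reason why local steroids were not widely adopted. The candidiasis comparison is therefore the safety result that readers will look for first, and a biased estimate of it would weaken any conclusion on the balance of benefit and harm.

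**Working it through.** **1. How the FAS can lose a candidiasis case.** Mucositis and candidiasis are recorded on the same occasions: at each post-allocation visit and again at termination or cancellation. The loss therefore depends on what it means for the primary endpoint to be obtained, which the protocol does not define.

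- If any post-allocation mucositis assessment is enough, almost everyone with a candidiasis record is also in the FAS, and little is lost.
- If a result over the full 8 weeks is needed, a treated participant who has candidiasis and leaves early without mucositis is excluded, although the date of the candidiasis is known. A Kaplan-Meier analysis does not need this exclusion, because it can censor incomplete follow-up.

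**2. How the PPS can lose a case.** Under the criteria for protocol treatment, a betamethasone participant who keeps gargling despite candidiasis deviates, and so does an azulene participant who stops because of it. Removal is possible in both arms, under opposite rules. In addition, the section on foreseeable disadvantages says that betamethasone gargling is stopped at once when such a side effect arises, without mentioning resumption. A participant who suspends and resumes follows one section and may breach the other, so PPS membership of betamethasone cases is not determined.

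**3. How many participants could be involved.** The only planning figure is the dropout allowance in the sample size: "Using two tailed alpha of 0.2, a power of 0.8, and accounting for a 10% dropout rate". With 40% against 27%:

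- Uncorrected n per arm = [1.2816·√(2·0.335·0.665) + 0.8416·√(0.40·0.60 + 0.27·0.73)]² / 0.13² = 118.
- With continuity correction: 133.
- 133/0.9 = 147.8, so 148 per arm and 296 in total, which is the protocol's figure.

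The allowance is 148 − 133 = 15 per arm. It is an upper-range value here, because it assumes that every dropout gargled at least once and has no primary endpoint.

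**4. What that could do.** The candidiasis counts below are assumptions. Simple proportions are used: cases/148 in the treated set, remaining cases/133 in the FAS. Azulene cases are lost in proportion (cases × 15/148, rounded: 0 of 4, 1 of 7, 2 of 15). Only the number of betamethasone cases lost is varied.

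| Assumed cases, betamethasone vs azulene | Treated set: RR; difference | Betamethasone cases lost | FAS: RR | FAS: difference (points) |
|---|---|---|---|---|
| 7 vs 4 | 1.75; 2.0 | 0 / 1 / 2 / 4 | 1.75 / 1.50 / 1.25 / 0.75 | 2.3 / 1.5 / 0.8 / −0.8 |
| 15 vs 7 | 2.14; 5.4 | 0 / 2 / 4 / 8 | 2.50 / 2.17 / 1.83 / 1.17 | 6.8 / 5.3 / 3.8 / 0.8 |
| 30 vs 15 | 2.00; 10.1 | 0 / 3 / 8 / 15 | 2.31 / 2.08 / 1.69 / 1.15 | 12.8 / 10.5 / 6.8 / 1.5 |

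Example for 15 vs 7 with 4 and 1 lost: 11/133 = 8.3% against 6/133 = 4.5%, RR 1.83, difference 3.8 points. With losses close to proportional (2 and 1), the result hardly moves: 13/133 against 6/133, RR 2.17.

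**The case against.** The strongest reply is that little is lost in practice. The label of the Safety Analysis Set ties it to safety analysis, so the description of adverse events can be read as covering all treated participants, candidiasis included. A statistical analysis plan that is not shown may say so. Mucositis and candidiasis are recorded together, follow-up continues after discontinuation where possible, and cases with missing items are not to be discarded. Someone with no post-allocation visit has no candidiasis record either and would add nothing to the treated-set comparison.

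Most of this stands, and it limits the size. It does not remove the point: the formal comparison has a stated population and that population is not the treated set, while the rule on missing items does not override the FAS definition.

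Three stronger readings are tempting and are not supported:

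- **A reader might infer that the Safety Analysis Set serves no purpose.** Its label says otherwise; it is only that no analysis section names it.
- **A reader might infer that cases are lost mainly from the betamethasone arm.** Suspending as instructed is compliance with the treatment criteria. An azulene user who stops because of candidiasis also deviates, and nothing in the protocol shows which deviation would be more common.
- **A reader might infer that the harm will be understated.** The table shows movement both ways. The large reductions need betamethasone cases to be heavily over-represented among those lost, for example 8 of the 15.

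**Conclusion.** The point holds in a limited form. The only between-arm comparison of a listed safety endpoint is assigned to two sets that can exclude treated participants with the event, possibly unevenly by arm, although a suitable set is already defined. The bias may go either way, including toward understating the harm.

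Its size cannot be stated, because the protocol gives no candidiasis rates. In the middle assumed example, a risk ratio of 2.14 in the treated set becomes 1.17 to 2.50 in the FAS. That range rests on invented counts and on the full dropout allowance of 15 per arm being treated but outside the FAS. If any single post-allocation mucositis assessment qualifies for the FAS, the effect there would be small, and the PPS would remain the weaker set. This is a free improvement, not a flaw that endangers the trial.

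**What to change.** In the analysis of secondary endpoints and the analysis of safety assessment, state that:

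- the candidiasis comparison and the adverse-event summary use the Safety Analysis Set, with time counted from first gargle;
- participants without a mucositis result are kept and censored at their last oral assessment;
- an FAS analysis of candidiasis is supportive only, and the PPS is not used to draw a conclusion on this harm.

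Separately, reconcile the treatment criteria (suspend and resume) with the section on foreseeable disadvantages (stop at once), because together they determine who counts as a deviator. Which rule is right is for the investigators.

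The cost is a few lines of wording in a protocol revision. No additional participants, visits or data items are needed, since candidiasis and its onset are already collected at each visit and at cancellation, and the sample size is unaffected.
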